# Trial protocol: a clustered, randomised, longitudinal, type 2 translational trial of alcohol consumption and alcohol-related harm among adolescents in Australia

**DOI:** 10.1186/s12889-018-5452-3

**Published:** 2018-04-27

## Abstract

**Background:**

This cluster randomised control trial is designed to evaluate whether the Communities That Care intervention (CTC) is effective in reducing the proportion of secondary school age adolescents who use alcohol before the Australian legal purchasing age of 18 years. Secondary outcomes are other substance use and antisocial behaviours. Long term economic benefits of reduced alcohol use by adolescents for the community will also be assessed.

**Methods:**

Fourteen communities and 14 other non-contiguous communities will be matched on socioeconomic status (SES), location, and size. One of each pair will be randomly allocated to the intervention in three Australian states (Victoria, Queensland and Western Australia). A longitudinal survey will recruit grade 8 and 10 students (M = 15 years old, *N* = 3500) in 2017 and conduct follow-up surveys in 2019 and 2021 (M = 19 years old). Municipal youth populations will also be monitored for trends in alcohol-harms using hospital and police administrative data.

**Discussion:**

Community-led interventions that systematically and strategically implement evidence-based programs have been shown to be effective in producing population-level behaviour change, including reduced alcohol and drug use. We expect that the study will be associated with significant effects on alcohol use amongst adolescents because interventions adopted within communities will be based on evidence-based practices and target specific problems identified from surveys conducted within each community.

**Trial registration:**

The trial was retrospectively registered in September, 2017 (ACTRN12616001276448), as communities were selected prior to trial registration; however, participants were recruited after registration. Findings will be disseminated in peer-review journals and community fora.

## Background

Community-led interventions that systematically and strategically implement evidence-based programs have been shown to be effective in producing population-level behaviour change, including reduced alcohol and drug use. Australian guidelines recommend that adolescents should not consume alcohol before they are 18 years but 44% do, with 34% reporting use in the last 30 days [1]. Community interventions such as the “Communities That Care” prevention framework have the potential to reduce these adolescent alcohol consumption (CTC; [2–4]. The CTC framework can be used to mobilise community stakeholders and organise them to work strategically to prevent the development of harmful behaviour patterns. Communities are supported to utilise local data to identify priorities and then to plan the implementation of interventions that have been found to be effective in previous evaluations.

Large community trials in the United States of America (USA) reveal that CTC can increase community implementation of evidence-based prevention interventions and reduce health-risk behaviour patterns among teenagers, resulting in reductions of between 15% - 25% in the prevalence of youth problems [2, 4]. Economic evaluations also indicate that CTC is worthwhile investment. Conservative estimates suggest CTC can produce a return on investment of approximately US$10.23 for every dollar [5, 6]. Over ten years, pilot work developing CTC in Australia has facilitated recruitment and training of community coalitions to plan and implement evidence-based programs. This work has demonstrated feasibility of CTC in Australia. Pilot studies have shown the CTC approach has been successfully implemented with fidelity and has been associated with reductions in teenage alcohol and drug use in line with those achieved in the USA (i.e. 15%) [7]. This study will employ a Type II translational randomised control trial to evaluate the effectiveness of CTC in Australia.

The primary outcome will be the proportion of secondary school age adolescents who use alcohol before the Australian legal purchasing age of 18 years. Based on pilot work done in Australia and CTC trial work done in the USA, we hypothesise that: compared to control communities, participants in intervention communities will maintain at least a 15% lower rate of frequent (last 30 days) youth alcohol use throughout the secondary school age period (primary outcome).

Secondary outcomes are other substance use and antisocial behaviours and the long-term economic benefits of reduced alcohol use by adolescents for the community. Overall, the research objectives for the trial are as follows:To deliver evidence-based alcohol-use prevention interventions in secondary schools as well as evidence-based community interventions targeting parents and teenagers, targeting teenagers aged 12 to 18.To evaluate the intervention using a longitudinal cohort survey and an analysis of archival and prospective health, crime and education records (routine service data).To conduct a process evaluation to assess intervention implementation and mechanisms of action.To estimate the economic benefits of reducing population rates of secondary school age alcohol use.To report on the cost-benefit of the intervention from a number of perspectives, using both trial-based and modelled economic methods.

## Methods

### The communities that care intervention

There are five phases to the CTC framework; these provide structure and benchmarking intervention implementation, monitoring and evaluation steps and processes (see https://www.communitiesthatcare.org.au/5-phases-ctc). In intervention communities, a lead agency (e.g. a Local Council) will be identified and required to lead the community through the phases, receiving a small grant on initiation of each phase. Standardised training sessions for each of the five phases will be delivered and a trained community relations officer appointed in each of the intervention communities.

Three strategies will be employed in intervention communities.

Brief Communication in Schools have been shown to be effective in reducing alcohol consumption [8]. This strategy targets teenagers and their parents and will be delivered during 3 school classroom lessons, promoting the following three messages:Based on scientific evidence, the National Health and Medical Research Council (NHMRC) guideline recommends that children should not drink before the age of 18.It is protective for teenagers if there is a household rule set by parents that they should not drink alcohol or be provided with alcohol before the age of 18.It is illegal for adults to serve alcohol to children that are not their own without written or verbal consent from the child’s parent or guardian.

Between lesson 2 and 3 leaflets highlighting these messages will be sent to parents/guardians and adolescents will be encouraged to discuss the content of these leaflets with adults in their home. The manual for this intervention component can be obtained from the research team.

2. Community-Based Sales Monitoring. Role-play shoppers will be selected by an expert panel to look younger than 18 years old and asked to purchase alcohol from community outlets. Best practice involves asking for age verification for anyone who looks under the age of 25 years. Feedback letters will be sent to outlets in the form of a letter, informing them of practice in their stores. This will clarify that the strategy is not intended to entrap but to monitor practice and encourage best practice and, moreover, that repeated failure to employ best practice will result in referral to licencing authorities. This strategy has been found to reduce alcohol sales to teenagers [9]. The manual for this intervention component can be obtained from the research team.

### Study design and data collection

The study will employ a Type II, translational, longitudinal, randomised control trial to evaluate CTC. Fourteen pairs of communities (clusters) matched on socio-economic status (SES), location, and size from three Australian states (Victoria, Queensland and Western Australia) will be recruited and one of each pair will be randomised to the CTC intervention or a no-intervention control. Intervention sites can be obtained from the research team, control sites will be available after the trial is complete.

### Participants and research eligibility

The primary hypothesis will be tested using a longitudinal school survey. Three waves of data will be collected; pre-intervention (baseline), and two waves post-intervention (see Fig. 1, Flow diagram).

**Fig. 1 Fig1:**
[figure not shown]
Flow chart estimating the progress of communities, schools and participants through trial. Trial registration: ACTRN12616001276448. *Wave 1 will be with either year 8 & 10, or Year 9 and 11, depending on speed in which communities work through the CTC phases, and the ease in which ethics is approved in the relevant school jurisdictions, and thus when the subsequent collection of survey data can occur. Final wave will be with year 11 students and 1 year post school. ** Approximate estimate of sample size of longitudinal cohort after 80% retention rate

Two secondary schools from each of the 28 communities will be invited to participate. Informed consent of school leaders will be required for school participation and if a school declines a nearby school will be approached. The survey will include items that assess alcohol use, and other related-behaviours as well as risk and protective factors (see measures below).

Students in the participating schools will be invited to complete the survey if they satisfy the following inclusion criteria:Are in the relevant (either Year 8 or 10) secondary school classroom grades (average age Grade 8 = 14 years; Grade 10 = 16 years);Have signed informed consent from their parents; andHave provided individual assent.

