### Sample size

Previous data indicate the intraclass correlation coefficients (ICC) for alcohol consumption in the last 30 days at community and school levels were .01 and .05, respectively. We calculated the required sample with power 0.8, type I error 0.05 and design effects based on clustering effect (ICC) at community, school and classroom clustering ranging from 0.1 to 0.01. Recent Australian secondary school survey data [10] indicate rates of alcohol use in the past month were 22% in grade 8 (average age 14) and 48% in grade 10 (age 16) (combined average 35%). Assuming 65% of parents consent to their child participating, we will request informed consent from 5400 to recruit 3500 students in 2017 (wave 1). These cohorts will be resurveyed at two time points after the intervention is delivered. Assuming an 80% retention rate, the hypothesised 15% reduction can be detected with 2800 participants in the longitudinal analyses. The research team will work with communities and relevant stakeholders to recruit schools for the study. Primary outcome data will be collected in the school setting using the CTC youth survey.

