### Statistical analyses

Intention-to-treat analyses will be employed. To account for within-individual variation we will employ repeated measures models with split-plot in time design matrix with binary outcome and logit link. Model parameters will be estimated using generalised estimating equations (GEEs) accounting for correlation within participants with an exchangeable working correlation matrix. For continuous secondary outcomes, GEEs with a Gaussian distribution and identity link will be implemented.

To assess the impact of the intervention on primary and secondary outcomes, time by treatment interactions will be examined in a model that includes the fixed categorical effects of assessment time, group indicator and treatment by group interaction. Trend effects due to staggered rollout of the intervention will be assed using models with a fixed effect categorical factor for year of treatment.

Clustering effects for schools and communities will be evaluated by calculating ICC and, if necessary, a series of (generalised) linear mixed models accounting for *clustering* (within participant/class/school/community). Analysts will not be blind to the communities that have been allocated to either intervention or control.

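### The Fig. 1 legend lets baseline school grade depend partly on intervention progress while the final grade is fixed, so age at baseline could differ by arm and distort the time-by-treatment interaction

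*Protocol article*

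**What the plan says.** The Fig. 1 legend makes the baseline grade conditional: "Wave 1 will be with either year 8 & 10, or Year 9 and 11, depending on speed in which communities work through" the CTC phases. The same sentence adds a second determinant, "the ease in which ethics is approved in the relevant school jurisdictions, and thus when the subsequent collection of survey data can occur". The end point is not conditional: "Final wave will be with year 11 students and 1 year post school".

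The inclusion criteria under Participants and research eligibility admit only the first option: "Are in the relevant (either Year 8 or 10) secondary school classroom grades". The abstract likewise recruits grades 8 and 10, in 2017.

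The section on the intervention places the phases in one arm: "In intervention communities, a lead agency (e.g. a Local Council) will be identified and required to lead the community through the phases". Under Study design and data collection, "one of each pair will be randomised to the CTC intervention or a no-intervention control".

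Under Statistical analyses, impact is judged by time-by-treatment interactions in "a model that includes the fixed categorical effects of assessment time, group indicator and treatment by group interaction" (I read the last term as time by group). No term for grade, age or time since baseline is named. A factor for year of treatment is planned, but for staggered rollout.

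**The concern.** One of the two stated drivers of baseline grade, progress through the CTC phases, exists in the intervention arm only. Table 1 puts the first survey in a post-allocation column (2017/18), so the choice of grade can follow allocation, and randomisation does not balance what happens afterwards.

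Alcohol use in the last 30 days rises steeply with school grade. Suppose some intervention communities start a grade older and every community finishes at the same grades. The intervention arm then shows a smaller rise from first to last wave even if the programme does nothing, and an interaction that takes wave 1 as reference counts that as benefit. An older control baseline would do the reverse and hide a benefit or suggest harm.

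**Working it through.** **Inputs.** Sample size section: "rates of alcohol use in the past month were 22% in grade 8 (average age 14) and 48% in grade 10 (age 16"); the two grades together are put at 35%. Background: a 15% lower rate, read here as relative. Random allocation: 14 communities per arm. Fig. 1 legend: the two baseline options and the fixed final grades.

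**1. The plan's own figures.** (22 + 48)/2 = 35%, as stated. The target is 0.15 × 35 = 5.25 points, that is 35% to 29.75%. As an odds ratio: (0.2975/0.7025)/(0.35/0.65) = 0.79.

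**2. Length of follow-up.** Year 8 to Year 11, and Year 10 to one year after school, are both 3 years. Year 9 to Year 11, and Year 11 to one year after school, are both 2 years. A later start shortens follow-up by one year.

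**3. Value of one grade.** Linear: (48 − 22)/2 = 13 points per grade. A Years 9 and 11 baseline would then have about 35 + 13 = 48%. On the logit scale the slope is [logit(0.48) − logit(0.22)]/2 = 0.593 (odds ratio 1.81 per grade). That gives about 34% in grade 9 and 63% in grade 11, again averaging about 48%. The grade 9 figure is interpolated and the grade 11 figure extrapolated.

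**4. Spurious interaction.** Assume no true effect, all controls at Years 8 and 10, and k of 14 intervention communities one grade later. At the final wave grades are equal, so the between-arm odds ratio is 1. The final-versus-baseline ratio of odds ratios is then control baseline odds divided by intervention baseline odds.
- Linear: intervention baseline p = 0.35 + 0.13 × k/14; ratio = (0.35/0.65)/(p/(1 − p)).
- Logit: ratio = exp(−0.593 × k/14).

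| k of 14 (assumed) | Baseline shift | Ratio, linear | Ratio, logit |
|---|---|---|---|
| 0 | 0 points | 1.00 | 1.00 |
| 2 | 1.9 points | 0.92 | 0.92 |
| 4 | 3.7 points | 0.85 | 0.84 |
| 7 | 6.5 points | 0.76 | 0.74 |

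**5. Shift equal to the target.** 14 × 5.25/13 = 5.7 communities. If the true gap per grade were 10 or 8 points (assumed), 14 × 5.25/10 = 7.4 or 14 × 5.25/8 = 9.2 communities.

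**6. A harder benchmark.** The interaction is read when students are older. At the linear Year 11 rate of 61%, a 15% relative reduction is 0.15 × 61 = 9.15 points, with odds ratio (0.5185/0.4815)/(0.61/0.39) = 0.69. On the log scale, the linear ratios for k = 4 and k = 7 are about 43% and 74% of that target. Against 0.79 they are about 66% and 115%.

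**7. Dates side by side.** Three years from 2017 is 2020, which is Table 1's last survey year and fits the legend's final grades. The abstract's last survey is in 2021, four years on, when students from Years 8 and 10 would be in Year 12 and two years past school. The Sample size section puts wave 1 in 2017, and Registration, ethics and data management puts it in February 2017; Table 1 shows 2017/18.

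The calculation covers only the final wave against wave 1, because the legend does not fix the wave 2 grade.

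**The case against.** A reader might infer that slow CTC progress delays wave 1 in the intervention arm and not in its controls, so that the comparison is already biased. The documents do not support that. The legend also names ethics approval, which is not arm-specific on its face and could delay both arms alike. It captions a chart of estimated progress for the whole trial and does not say whether the choice of grade is made per community, per pair or once for all. A pair-wise or trial-wide choice removes the imbalance. Several statements also point to a common baseline: the abstract recruits grades 8 and 10 in 2017, and the registration section reports the first wave as collected in February 2017. Table 1's 2017/18 leaves this unsettled.

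The fixed final grade is partly protective. A comparison of arms at the final wave alone would not be distorted by baseline age, and the Background hypothesis of a rate kept 15% lower can be read that way. The numbers of delayed communities have no source in the protocol. A condensed article may leave covariates to the analysis plan, so the lack of a listed grade term is not in itself an error.

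All of this stands, and it makes the bias conditional. It does not remove the stated rule, the contradiction with the inclusion criterion, or the fact that the stated test is an interaction with baseline as reference. The year-of-treatment factor and the subgroup analysis by age do not adjust for baseline grade.

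**Conclusion.** The contradiction is certain: the legend permits Years 9 and 11 at wave 1, and the inclusion criterion and abstract do not. The bias is possible but not shown. It requires that grade be set community by community, that more intervention than control communities start late (or the reverse), and that the primary model carry no grade or age term.

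Under those conditions a one-grade shift is worth about 13 points, roughly 2.5 times the 5.25-point target at the 35% base rate. With no delayed controls, 2, 4 or 7 late intervention communities give about 0.92, 0.85 or 0.75 where the truth is 1. The artefact is smaller relative to a target set at an older age, and zero if all sites, or both members of each pair, are surveyed in the same grades. The point should be fixed because the possible artefact is comparable in size to the effect sought and the remedy is cheap.

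**What to change.** - State that survey grades and survey window at every wave are the same for both members of a matched pair, whatever the intervention community's progress through CTC.
- Reconcile the Fig. 1 legend, inclusion criterion, abstract and Table 1 on baseline grades, final grades and survey years.
- Include grade (or exact age) at each survey, and time since baseline, in the primary model rather than wave number alone.
- If wave 1 is already collected, it cannot be rescheduled. Report baseline grade by arm and by pair, adjust as above, and apply the pair rule to the remaining waves.

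The cost is slight: some later control surveys may have to move, and the model gains a covariate already known, since grade is an eligibility criterion.

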### Data collection in control communities

The control communities will be observed using: (1) the longitudinal school survey with 3 waves of data (see Fig. 1, flow); (2) monitoring of underage alcohol sales and (3) and archive record assessments. See schedule of enrolment and measures in Table 1.

**Table 1 Tab1:** Schedule of enrolment, intervention and assessments

		STUDY PERIOD					
	Enrolment	Allocation	Post-allocation				Close-out
TIMEPOINT	*2016*	2017	*2017/18*	*2018/19*	*2019*	*2020*	*2020*
Cluster randomization	X						
Eligibility screen		X					
Informed consent		X					
Allocation		X					
INTERVENTIONS:							
* Brief communications in Schools*				X			
* Sales Monitoring*				X			
* Control*							
ASSESSMENTS:							
* Communities That Care Youth Survey*			X		X	X	X
* Community level archival data*			X		X	X	X

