### Random allocation

The community sampling frame was initiated by selecting all Statistical Local Areas (SLAs) with greater than 17,000 inhabitants across the Australian States of Victoria, Queensland, and Western Australia. These SLAs were stratified into quartiles of socioeconomic disadvantage based on Socio-Economic Indexes for Areas (SEIFA) [18, 19]. Thirty eligible communities were randomly selected from SEIFA quartiles to represent state distributions in advantage/disadvantage and urban and nonurban locations. Of the 30 originally sampled SLAs, two were excluded from the present study due to their prior involvement in the CTC approach (see Fig. 1). The remaining 28 SLAs were paired based on SEIFA scores, urban or nonurban locations and size. An independent statistician using a computerised random number generator, allocated one of each pair to the intervention and control group, resulting in 14 intervention and 14 control SLAs, and was blind to allocation sequence.

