### Registration, ethics and data management

The Trial is registered with the Australian and New Zealand Clinical Trial Registry (http://www.anzctr.org.au/; ACTRN12616001276448). The trial team started to develop relationships with community stakeholders in January, 2016, in order to build community capacity to implement the CTC framework. As community relationships were initiated, in September, 2016, the trial was retrospectively registered. The first wave of the trial and longitudinal data was collected in February, 2017.

There are no predetermined criteria for discontinuing or modifying the trial. No anticipated adverse consequences are anticipated for trial participants. In the case of any occurrence, details will be forwarded to Deakin University’s Human Research ethics committee, in accordance with the conditions of the ethics approval for the project. The current protocol (version 1) is in keeping with the current ethics approval. Any protocol modification will be, where appropriate, referred to Deakin University’s Human Research Ethics Committee and communicated through the trial registration listed in the Australian New Zealand Clinical Trials Registry.

Data management will be primarily the responsibility of the research team based at the School of Psychology, Deakin University. Management of trial data will be in accordance with a data-management protocol, which has been developed and approved by the Project Advisory Group, and available on request. The study protocol details requirements regarding data entry, data cleaning, data back-up, secure storage and transport, and analysis. The Deakin University Human Research Ethics Committee (DUHREC) has approved the project with the expectation that data will be securely stored, and accessible only to primary researchers and statisticians through allocation of access rights. Ethics approval number from DUHREC is 2,015,261.

Confidential data on school and community contact details (e.g. phone numbers, email addresses) will be stored in a secure dataset that is not linked to survey response datasets. A trained research manager will be the only person with access to confidential participant data. The National Health and Medical Research Council (NHMRC) is the primary funder of the trial (see https://www.nhmrc.gov.au/). The NHMRC will have no role in the implementation or management of the intervention, collection, management, analysis or interpretation or the publication of the trial data.

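### Schools and students are recruited after communities are randomised, with no stated blinding of recruiters and a loose replacement rule, so entry into each arm can depend on allocation

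*Protocol article*

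**What the plan says.** **Order of events.** Under Random allocation, the protocol article reports as already done that an independent statistician "allocated one of each pair to the intervention and control group, resulting in 14 intervention and 14 control SLAs, and was blind to allocation sequence". Table 1 (Data collection in control communities) marks the row "Cluster randomization" under 2016, and the eligibility and consent rows under 2017. A separate row, Allocation, is also marked under 2017. Registration, ethics and data management says: "The trial team started to develop relationships with community stakeholders in January, 2016, in order to build community capacity to implement the CTC framework". The same section dates the first survey wave to February 2017.

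**Recruitment of schools.** Two schools per community are to be invited (text below Fig. 1). The rule on refusal is: "Informed consent of school leaders will be required for school participation and if a school declines a nearby school will be approached". The Sample size section adds: "The research team will work with communities and relevant stakeholders to recruit schools for the study". Study design and data collection says that the identity of the intervention sites is available from the research team.

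**Recruitment of students.** Each student needs parental consent and individual assent. Sample size assumes that 65% of parents agree.

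**Analysis.** There is one pre-intervention wave and two later waves. The effect is tested as a time-by-treatment interaction in a model with "fixed categorical effects of assessment time, group indicator and treatment by group interaction". Neither grade nor the student's own wave 1 drinking is among the listed terms as a covariate; wave 1 drinking enters as one of the repeated outcomes.

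**The concern.** Randomising communities makes the arms comparable as communities. It protects the comparison of students only if schools and families then enter in the same way in both arms. Here both are approached after the randomisation, and the team that recruits schools is also the source of information on which sites receive the intervention. The only blinding mentioned at this stage is that of the statistician, who is not described as recruiting anyone. School leaders can decline, the replacement is defined only by being nearby, and about a third of invited families are expected not to take part. At each of these steps knowledge of the arm could influence who enters.

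If that happened, the arms would differ for reasons other than the intervention. Intention-to-treat analysis would not repair it, because it preserves the arms as recruited. The baseline wave helps, but only partly: students selected on early drinking, or on family attitudes to alcohol, can also follow a different course afterwards.

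**Working it through.** **1. The plan's own recruitment chain.** From Sample size: 5400 approached × 0.65 = 3510 (stated 3500), and 3500 × 0.80 = 2800 (stated 2800). The chain reproduces. About 35% of approached students do not enter, so there is room for selection.

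**2. Sequence.**

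| Event | Date | Section |
|---|---|---|
| Capacity-building with communities starts | January 2016 | Registration, ethics and data management |
| Cluster randomisation | 2016 | Table 1 |
| Eligibility screen, informed consent, Allocation | 2017 | Table 1 |
| First survey wave | February 2017 | Registration, ethics and data management |

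Because Allocation shares the 2017 column with consent, the date on which arms were disclosed is not clear. The order of randomisation before student consent is.

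**3. What the planned contrast leaves behind.** The planned test compares change over time on the logit scale, so the relevant bias is in that change and not in the gap at entry.

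Inputs from Sample size: 22% past-month use in grade 8, 48% in grade 10, 65% consent, 15% reduction (read as relative). Assumptions, not in the documents:
- There is no true effect, and the grade 8 cohort moves from 22% to 48% between waves.
- Overall consent is 65% in both arms. In the intervention arm only, drinkers' families consent at 60%.
- A baseline drinker drinks at follow-up with probability a = 0.7, 0.8 or 0.9. For a baseline non-drinker the probability is b, set so that the control arm reaches 48%: b = (0.48 − 0.22a)/0.78. Both are the same in the two arms.

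Baseline prevalence in the selected arm: 0.22 × 0.60/0.65 = 0.203.

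Baseline logit difference: logit(0.203) − logit(0.22) = −1.367 − (−1.266) = −0.102 (from unrounded values).

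Follow-up prevalence in the selected arm: f = 0.203a + 0.797b, to be compared with logit(0.48) = −0.080.

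| a | b | f | logit(f) − logit(0.48) | Residual contrast |
|---|---|---|---|---|
| 0.7 | 0.418 | 0.475 | −0.019 | −0.019 + 0.102 = 0.082 |
| 0.8 | 0.390 | 0.473 | −0.028 | −0.028 + 0.102 = 0.074 |
| 0.9 | 0.362 | 0.471 | −0.037 | −0.037 + 0.102 = 0.065 |

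**4. Set against the hypothesised effect.** At 48% prevalence a 15% relative reduction gives 0.48 × 0.85 = 0.408, and logit(0.408) − logit(0.48) = −0.372 + 0.080 = −0.292. The residual is 0.065/0.292 = 22% to 0.082/0.292 = 28% of it, with the opposite sign.

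**5. What adjustment would do in this example.** Given baseline drinking, follow-up probabilities are the same in both arms by construction. A comparison adjusted for wave 1 drinking therefore has no residual bias here. That holds only because selection was assumed to act through wave 1 drinking alone.

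**The case against.** The strongest reply is that the design already contains the main protection: a pre-intervention wave and a test of change over time. That stands for differences constant on the logit scale. It does not cover different trajectories, as the calculation shows.

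A second reply is that a condensed article may leave school lists, scripts and replacement order to a fuller protocol. That is fair for the detail. But the order of events, the recruiting team and the nearby-school rule are stated, and the point rests on those.

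A third is that wave 1 was collected from February 2017, before the article appeared in April 2018, so a new recruitment rule comes too late for many schools. This stands, and it limits the first half of the fix.

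Four stronger readings are tempting and are not supported:
- *Recruitment differs by arm.* A reader might infer this because intervention communities have a lead agency and a community relations officer. The article describes one recruitment process for the whole study and gives those roles no part in it.
- *Stakeholders choose the schools.* The text says only that the team works with them in recruiting.
- *Substitutes lie outside the randomised community.* The wording sets no boundary, but the sentence comes shortly after the one inviting two schools from each community. Replacement within the community is the natural reading, so a loss of power from out-of-area schools should not be claimed.
- *Bias could match the planned effect.* Gaps at entry can be made that large by assumption, but the planned test does not compare arms at entry.

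**Conclusion.** The point holds as a risk in the design. Recruitment of schools and students follows randomisation, no blinding of recruiters is stated, and the replacement rule leaves discretion, so entry can depend on allocation. The documents do not show that any bias occurred.

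The size is illustrative: a log odds ratio of 0.065 to 0.082 in the grade 8 contrast, 22% to 28% of the hypothesised -0.292. It rests on the assumed 60% versus 65% consent in one arm and on the assumed persistence of drinking. In that example the bias works against the intervention, so it does not by itself point to a false positive. The same selection in the control arm would reverse the sign. Selection on later trajectory, for instance of families motivated by the programme, is not removed by the baseline wave and could favour the intervention; its size cannot be derived from the documents.

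The change is worth making because it is cheap, not because a large bias has been demonstrated.

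**What to change.** **For any recruitment still open**, replace the refusal rule below Fig. 1 with: *A declining school is replaced only by the next school on a randomly ordered list of eligible schools in the same SLA, prepared by the independent statistician. Schools are approached with the same script and consent materials in both arms.*

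**For schools and students already recruited:**
- Add wave 1 grade to the primary model. The plan's own rates differ sharply by grade (22% versus 48%).
- Adjust the comparison at the post-intervention waves for the student's wave 1 30-day alcohol use.
- Report school refusals, school substitutions and parental consent rates by arm, so that readers can judge whether entry was similar.

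**Cost.** One protocol sentence, one list per SLA from a statistician already engaged, and two covariates collected at wave 1. Recruitment may be slightly slower, and an SLA whose list runs out may end with fewer than two schools. Covariate adjustment reduces selection bias but cannot fully remove it.
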